### Social science

Quantitative questionnaires in randomly selected students from four schools will be used to determine the main activities of children before and after school in terms of outdoor versus indoor behaviour, types of activities undertaken before and after school, and whether the school uniform is worn after school and for how long, including how the school uniforms are treated (washed and dried) between use. Furthermore, qualitative studies will be used in a small number of randomly selected students to evaluate the washing habits at home. Home visits will be done and key informant interviews conducted with those household members in charge of laundry washing. The purpose is to describe the main methods of washing, drying and ironing.

Movement of children will be assessed using brief questionnaires to estimate the time at risk and usage of the allocated uniforms.

### Risk mapping

Spatial clustering analysis of dengue infections will be carried out to determine transmission foci using geographical information systems (GIS). Locations of schools and study participant home residences will be mapped. Dengue cases will be reported geographically to detect potential hot spots or spatial transmission patterns.

### Analytical plan

The primary endpoint is a comparison of the incidence rates of laboratory-confirmed dengue infections per person-time exposed up to failure (i.e. dengue infection) or censoring (i.e. moving away) between the intervention and control groups.

### Safety considerations

There are no apparent risks to the safety of individuals or communities in this study. Due to its low toxicity and long-lasting efficacy, permethrin is one of the most commonly used insecticides in impregnated clothing. Low irritancy and odour also add to the popularity of permethrin-impregnated clothing [19]. Permethrin-treated uniforms have been fully evaluated by multiple governments for use in military uniforms, for example in the US, Germany and France [21,36]. Even though there is some absorption of the permethrin through the skin, the amount absorbed is well below the acceptable daily intake, and health side effects are not expected [13,37,38]. Insect Shield has met all health requirements for approval by the United States Environmental Protection Agency (USEPA) and has maintained these health standards since 2006 (Insect Shield USEPA, 2009). They are approved for vector control, and the products will be

used in compliance with their recommended use and guidelines.

Teachers will document any skin irritations initially every 2 weeks, then every 4 weeks during the study period. Should skin irritations occur, the students will be sent to the study medical clinics for further documentation by trained personnel. In the case that a participant develops a serious adverse event (SAE) during the course of the study, this will be captured in the case report form. In case of an SAE, the study physician will record and manage the SAE in accordance with Good Clinical Practice (GCP). Excessive clustering of SAE by school will be reported to the study's Data Monitoring and Safety Committee (IDMC). A determination by the IDMC that there is a potential harm to participants or the environment caused by the interventions will result in discontinuation of the study.

If an individual wants to terminate his/her participation, no further follow-up will be performed. In the case of a study child leaving during year 1, they will be replaced in year 2 of the study (May-June 2013). There will be no replacement during the surveillance period either year. If a school opts out of the study before July in either year, replacement by a neighbouring school will be considered.

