### Intervention

Routinely used school uniforms will be collected from all consenting children and treated with a long-lasting permethrin formulation, using a factory proprietary method. The process involves coating the uniforms in a proprietary formula containing 0.52% permethrin (Insect Shield USEPA2009). The technology claims to provide 80–96.7% knockdown after 70 washes [25]. Enrolled children will receive either permethrin impregnated or untreated school uniforms. For schools assigned to the control group, uniforms will be collected and washed using the same methodology as those used in the

treatment group, but without the impregnation process with permethrin.

School uniforms vary in form, colour and size. School uniforms include the regular school uniform, scouts uniform, sports uniform and cultural uniform. Most of the typical uniforms are short-sleeved and only cover the legs down to the knees (shorts or skirts). The variation between the schools is minimal for the uniforms, except for the cultural uniform.

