### Randomisation and blinding

There will be double-blinding: neither the children nor the investigators will know the allocation. School uniforms from Thailand will be sent to the InsectShield factory: one group will undergo washing and treatment with permethrin. The control group will only undergo washing. Both the impregnated and washed uniforms will be identified with labels indicating the child's name, school and year, but there will be no identifiable indication as to which uniforms are actually impregnated.

All participating schools will be stratified into two by enrolment size, above and below median. Randomisation to two groups (intervention followed by control, control followed by intervention) will be carried out in Sweden. This information will be kept confidential between one epidemiologist and the impregnation facility.

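### Ending a child's participation or the study does not by itself end contact with the treated uniforms, and the later course of an open skin reaction would go unrecorded

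*Protocol*

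**What the plan says.** Protocol, Safety considerations, gives two rules for ending things. An IDMC determination of potential harm to participants or the environment "caused by the interventions will result in discontinuation of the study". For a single child: "If an individual wants to terminate his/her participation, no further follow-up will be performed". The same section has teachers note skin irritation every two and later every four weeks within the study period, refers affected children to the study clinics for documentation, and has the study physician handle serious adverse events.

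Protocol, Intervention, describes the exposure: "Routinely used school uniforms will be collected from all consenting children and treated with a long-lasting permethrin formulation". On durability it adds: "The technology claims to provide 80–96.7% knockdown after 70 washes".

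Protocol, Randomisation and blinding, says that garments from both groups "will be identified with labels indicating the child's name, school and year", but that "there will be no identifiable indication as to which uniforms are actually impregnated". It also says that "neither the children nor the investigators will know the allocation", and of the allocation: "This information will be kept confidential between one epidemiologist and the impregnation facility".

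The clinical secondary objectives include the safety of the impregnated uniforms in children.

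**The concern.** In many trials, leaving or stopping ends exposure because the supply ends. Here the insecticide is bound into clothes that the child owns and wears to school almost every day. The two rules act on follow-up and on the study; neither mentions the garment.

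Two things are at stake. One is safety: a family that leaves because of a skin reaction cannot see whether the uniform is treated, and the protocol describes no step concerning it. The other is the safety data: whether a reaction resolved, persisted or worsened is part of the safety result, and the plan ends recording without exception, including for a child whose reaction is still open on leaving.

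**Working it through.** There is no planned figure to reproduce. The check sets the sections side by side, with two small calculations for scale.

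**1. What each rule ends, taken literally**

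| Event | Ends by the text | Not mentioned |
|---|---|---|
| Child ends participation | All further follow-up (explicit) | The uniform; the outcome of an open reaction |
| IDMC finds potential harm | The study (explicit); skin checks by inference, since they are tied to the study period | The uniforms; open reactions |

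**2. Does exposure end on its own?** Intervention supports that the uniforms are the children's own, because they are collected from the children; the words about pre-fabricated uniforms in the abstract and primary objective do not change this. On durability, the protocol's claim is 70 washes. It gives no wash frequency, so I assume a range:

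- 1 wash a week: 70 / 1 = 70 weeks
- 2 washes a week: 70 / 2 = 35 weeks
- 5 washes a week: 70 / 5 = 14 weeks

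Over that range the treatment could outlast a withdrawal by weeks to months. The claim concerns mosquito knockdown, not skin contact. The Discussion and Conclusion also say that local washing and drying may shorten the effect. The calculation shows only that leaving does not end exposure by itself.

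**3. Is the reaction already on record?** Usually yes. Teacher checks and clinic referral capture its occurrence before the child leaves. What the withdrawal rule removes is its later course.

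**4. Can treatment status be recovered?** Yes. Allocation is by school, labels carry school and year, and one epidemiologist and the factory hold the list. The sections reviewed describe no route for disclosure.

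**5. What would routine disclosure cost?** Each school has one of two sequences, so learning one child's status in one season gives the whole school's status in both. The plan has 2,012 children in ten schools, or 2,012 / 10 = about 201 per school on average. Its 20% dropout allowance gives 0.20 × 201 = about 40 leavers per school. Not all of these are withdrawals by choice, but a rule to disclose at each departure could unmask most or all schools.

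**6. How many children?** The planned treated group is 2,012 / 2 = 1,006 in a season. That is a ceiling on those in treated uniforms at a study stop. The document has no rate of withdrawal for skin reactions, so no estimate follows.

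**The case against.** The case against has real weight.

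- *The sections do not contradict one another.* Uniforms can be treated, allocation masked, and participation ended, all at once. This stands: on the uniforms the point is mainly one of missing detail. The consent text is not available, and it may tell families what to do with the garments. It does not answer the withdrawal rule, which is stated outright and without exception.
- *There are other responses to harm.* A reader might infer that discontinuing the study is the only one. That is wrong: the protocol also has clinic referral, management of serious adverse events by the study physician, reporting of clustering by school to the IDMC, and 24-hour reporting of serious effects to the ethics board. The serious-event provision, however, applies during the study and does not reach an open non-serious reaction in a child who has left.
- *Continued wear is not documented.* This stands. That children go on wearing treated garments is inferred from silence and the wash claim.
- *Unmarked does not mean unidentifiable.* A reader might infer that nobody could establish which garments are treated. Status is recoverable, and the labels let a family recognise every study-processed garment without knowing the allocation.
- *The protocol expects no side effects.* It does, but it still provides a stop for harm and names safety as an objective, so the provisions should work if needed.

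**Conclusion.** The point holds in a limited form. Followed literally, the withdrawal rule ends recording of an open skin reaction while the likely source, a long-lasting treatment in the child's own clothes, is not addressed. For a study stop the same gap is likely but inferred.

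Two stronger conclusions are tempting and unsupported. One is that skin effects in the treated season would be under-counted: occurrence is recorded before a child leaves, so what is at risk is information on duration and outcome. The other is a count of affected children. Supposing that 1 to 5% of 1,006 leave for irritation gives 10 to 50, but nothing in the document supports that rate.

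The conclusion assumes that the uniforms return to the child, as Intervention implies, and that no arrangement for them exists in text not available here. I would class it as a cheap improvement, not a flaw that threatens the primary result.

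**What to change.** 1. In Safety considerations, limit the end-of-follow-up sentence: a reaction that is open or suspected at withdrawal, or when the study stops, stays under safety recording if the family agrees.
2. Reconcile the clinical secondary objectives, Intervention, Randomisation and blinding, and Safety considerations on the status of the uniforms when a child's participation or the study ends. The clinical content is for the sponsor and the IDMC.
3. Do not make disclosure of allocation a routine step at each withdrawal. Whatever arrangement is chosen should treat all labelled study uniforms alike, treated or washed only, so that it reveals nothing about the school.

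The cost is protocol and consent wording, plus a little extra recording at the study clinics already in use. Sample size and the primary analysis are unchanged, and blinding is preserved if the third item is kept.

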### Ethical considerations

This study is conducted in accordance with the principles set forth in the International Conference on Harmonization Tripartite Guideline of Good Clinical Practice and the Declaration of Helsinki. The study was approved by the Thai Ethics Review Board. Using a crossover, school-randomised design means that every individual will be equally exposed to the risks of dengue infection and to possible benefits of the intervention, taken over the entire trial period. Serious adverse effects of wearing the impregnated clothes will be reported to the Ethics Review Board within 24 h.

### Discussion

Reducing the incidence of dengue in school children not only reduces morbidity and mortality, but also reduces the number of school days lost, increases school performance and reduces the economic burden on parents. If our study proves that impregnated school uniforms reduce dengue infections in children, this would be a novel, simple and cost-effective intervention that is feasible, safe and scalable in resource-limited countries. Moreover, it should be community-based. However, if the null hypothesis is not rejected, then we have to elaborate on reasons why the intervention did not work. Potential reasons could be that the time an impregnated school uniform is worn during the day is not sufficiently long to protect against mosquito bites. Furthermore, the

exposure to mosquito bites could possibly be higher during the daytime after school activities. Lastly, the waning of the knockdown effect of impregnated uniforms may be enhanced through washing and drying techniques in tropical countries that are different to those used in Western countries.

### Conclusion

This is a community effectiveness trial. Although a significant knockdown and repellence effect of impregnated clothing has been reported under 'ideal' conditions (efficacy), this needs to be tested in 'real life' under field conditions (effectiveness). There will be many confounding factors that will have an impact on the risk of transmission, for example, school uniforms typically do not cover the full body, they are not worn all day long, they are usually not worn during weekends and holidays, and lastly, the washing conditions in tropical countries (frequency of washing, drying in the sun, aggressive detergents, etc.) may expedite the waning of the knockdown effect over time.

### Trial status

The trial and enrolment at the time of submission.

### Competing interests

The authors declare that they have no competing interests.

### Acknowledgements

DengueTools is funded under the Seventh Framework Programme of the European Community, Grant Agreement Number: 282589 Dengue Tools.

**Submit your next manuscript to BioMed Central and take full advantage of:**

- **Convenient online submission**
- **Thorough peer review**
- **No space constraints or color figure charges**
- **Immediate publication on acceptance**
- **Inclusion in PubMed, CAS, Scopus and Google Scholar**
- **Research which is freely available for redistribution**

Submit your manuscript at  
www.biomedcentral.com/submit

[figure not shown]

Supplement: S1 Trial Protocol — (PDF) [file pntd.0005197.s002.pdf]
